#### Secondary objective

The secondary objective is to compare the mean changes of anthropometric data (weight, height, waist circumstance (WC), hip circumstance (HC), body mass index (BMI), waist-height ratio (WHtR), waist-hip ratio (WHR), fat mass (FM), free fat mass (FFM), muscle mass (MM), and A Body Shape Index (ABSI)), physical activity (PA), diastolic blood pressure (DBP), systolic blood pressure (SBP), serum alanine transaminase (ALT), serum aspartate enzyme transaminase (AST), health-related quality of life (HRQOL), and dietary intake between the groups.

### Hypothesis

Curcumin and zinc co-supplementation will significantly improve the serum levels of biochemical parameters, anthropometric data, HRQOL, PA, and BP in prediabetic patients.

### Trial design

We designed a single-center, double-blinded, randomized placebo-controlled clinical trial among patients with prediabetes with a convenience sampling technique.

## Method

### Study design

The flow chart of the study design and the schedule of enrollment, interventions, and assessments are shown in Figs. 1 and 2, respectively. The participant will be randomized in a 2 × 2 factorial design into four parallel treatment groups: (1) curcumin group (Cur/P.Zn), curcumin supplement + placebo for zinc; (2) zinc group (Zn/P.Cur), zinc supplement + placebo for curcumin; (3) zinc + curcumin group (Zn/Cur), zinc supplement + curcumin supplement; and (4) placebo group (P.Zn/P.Cur), placebo for curcumin and zinc. The follow-up duration will be 3 months (90 days).

**Fig. 1 Fig1:**
[figure not shown]
Study design flow chart. RCT, randomized controlled trial; IPAQ-SF, Short Form of International Physical Activity Questionnaire; SF-36, Short Form 36 Questionnaire

**Fig. 2 Fig2:**
[figure not shown]
Schedule of enrollment, interventions, and assessments. ABSI, A Body Shape Index; AST, aspartate aminotransferase; ALT, alanine aminotransferase; BCM, beta cell function; BMI, body mass index; DBP, diastolic blood pressure; FFM, free fat mass; FM, fat mass; FPG, fasting plasma glucose; HC, hip circumference; HbA1c, hemoglobin A1c; HDL, high-density lipoprotein cholesterol; HOMA, homeostasis model of assessment; HRQOL, health-related quality of life; hs-CRP, high-sensitivity C-reactive protein; IL-1B, interleukin-B; IPAQ-SF, Short Form of International Physical Activity Questionnaire; IR, insulin resistance; IS, insulin sensitivity; LDL, low-density lipoprotein cholesterol; MDA, malondialdehyde; MM, muscle mass; HTN, hypertension; SBP, systolic blood pressure; TAC, total blood antioxidant capacity; TTC, total cholesterol; TG, triglycerides; VLDL, very low-density lipoprotein; WC, waist circumference; WHR, waist-hip ratio; WHtR, waist-height ratio; 2hpp, 2 h post-prandial

This trial dated 05 October 2019 was approved by the Medical Ethics Committee of Ahvaz Jundishapur University of Medical Sciences, Ahvaz, Iran (ethical code: IR.AJUMS.REC.1398.504; available on site: http://ethics.research.ac.ir/IR.AJUMS.REC.1398.504), and it is a prospectively registered clinical trial (registration number: IRCT20190902044671N1, Iranian Registry of Clinical Trials (IRCT), available on site: https://en.irct.ir). The study will be reported according to the Consolidated Standards for Reporting Trials (CONSORT) statement (http://www.consort-statement.org/, accessed 14 April 2017). The present study will be conducted at the Diabetes Research And Clinical Practice Center of Yazd, Central Iran, where the prevalence rate of diabetes is higher than in other parts of the world [43].

### Participants

The subjects are introduced to the trial, and those who are interested to know more are invited via email, phone call, SMS, or social media (Telegram or WhatsApp) to the study center, where the study investigator explains the study in detail to the subjects. After the clarifications have been provided, the subject will be asked to voluntarily sign the consent form (Supplementary Material, Table S3), and the first appointment will be booked. In the first appointment, the consented subjects undergo screening procedures for the study under an endocrinologist according to the ADA guidelines. The eligible subjects will be enrolled in the trial and randomized to the appropriate study groups. The screening period is planned for 12 months and will continue until 84 participants are randomized in the study.

### Inclusion/exclusion criteria

#### Inclusion criteria

Women or men (18–50 years old for men and 18 years to before menopause for women) with prediabetes according to the ADA guidelines [2] (FPG ≥ 100 and < 126 mg/dl, IGT ≥ 140 and < 200 mg/dl, 2-h plasma glucose concentration after a 75-g glucose load on the oral glucose tolerance test (OGTT) ≥ 140 and < 200 mg/dl, or/and HbA1c 5.7–6.4%) and BMI between 25 and 35. Voluntary written informed consent for all patients is mandatory before any study-related procedures.

#### Exclusion criteria

The participants must not have any of the following: a diagnosis of any types of malignancies and cancers, chronic or acute hepatic disorders (hepatitis B and C, etc.), bile disease, autoimmune diseases, neurological diseases (such as epilepsy), neurological diseases, effective hereditary disorders of the liver (iron and copper storage disease), endocrine diseases (hypothyroidism, hyperthyroidism, and Cushing’s syndrome), inflammatory diseases (rheumatoid arthritis), hypertension, cardiovascular, acute or chronic kidney disease, and lung disease; taking blood pressure-, glucose-, or lipid-lowering drugs (e.g., insulin, metformin, Glucophage, or atorvastatin); taking multivitamin-mineral supplements for 3 months before or during the intervention; a history of weight loss surgery in the last year and a weight-loss plan in the last 3 months; receiving a weight-loss medicine or program; lactating, pregnant, or planning to get pregnant; a history of any condition that the investigator may consider a contraindication to participation (such as the sensitivity to supplementation or simultaneously participating in another project); unwillingness to continue cooperation, non-compliance during the intervention (compliance less than 80%); or no signed informed consent.

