### Sample size

The sample size was determined based on the ability to detect a mean effect of FPG between the supplement and placebo groups for each supplement (curcumin or zinc), separately.

By using the following formula, the maximum sample size for curcumin group based on the trial by Chuengsamarn et al. [26] and zinc group based on the trial by Ranasinghe et al. [40] was determined to be 8 ($$ {\overline{X}}_1 $$ = 3.64, $$ {\overline{X}}_2 $$ = − 7.54, *S*_1_ = 8.17, and *S*_2_ = 7) and 19 ($$ {\overline{X}}_1 $$ = + 16, $$ {\overline{X}}_2 $$ = + 3, *S*_1_ = 12.8, and *S*_2_ = 15.3), respectively (*α* = 0.05, significance; *β* = 0.2, power). Then, the maximum sample size was considered as the final sample size, which is sufficient to evaluate the main effects. According to an expected 10% loss at follow-up, 84 subjects (21 participants in each group) will be recruited, finally.

$$ {n}_1=\frac{\left({S}_1^2+{S}_2^2\right){\left({Z}_{1-\frac{\alpha }{2}}+{Z}_{1-\beta}\right)}^2}{{\left({\overline{X}}_1-{\overline{X}}_2\right)}^2} $$

In the formula above, *S*^2^ and $$ \overline{X} $$ show the variance and the mean effect for FBS in the placebo and treatment groups, respectively. Also, for a more accurate calculation of the sample size, the WinPepi statistical program (version 11.4: Abramson, 2011) was performed.

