### Randomization and blinding

The randomization of the participants for this study will be conducted using the method of block randomization with a block size of 4 using a computer-generated random number sequence by one of the research staff (who is an independent statistician and not available to the study investigators or the study staff). Then, the allocation concealment will be conducted assigning the unique codes in order to prevent “selection bias,” and it will be maintained by the pharmacist who is a research staff not involved during the study (the pharmacist is involved only with the dispensing of the investigational products). After checking the inclusion and exclusion criteria and the baseline measurements by two investigators, the eligible participants will be given consecutive numbers, which will be forwarded to the pharmacist who will dispense the interventional product. The pharmacist will open the sealed envelope (that is given by the independent statistician containing the treatment code) after the final data analysis and/or an emergency situation. All the assessments in the trial will be made by the investigators blinded to the treatment allocation. In the event of an emergency situation where being aware of the treatment allocation is critical, the pharmacist will be accessed to unblinding envelopes provided for each participant. Further assessment and required medical or legal interventions will be carried out according to the case. The emergency unblinding and the reason should be recorded in the case report form. The treatment code would be communicated to the medical personnel in charge of the treatment but should not be recorded or verbally disclosed in any of the study documents or to the patient. Since this is a double-blinded study, the investigators, participants, and those involved in the study will not be informed about the type of supplement used except the research staff. The supplements will be delivered to the participants according to the allocation on the 1st, 30th, and 60th days.

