### Participant adherence

At each follow-up visit, (1) participants will be briefed on the study guidelines (dietary and PA recommendation), adherence to the dosing schedule, dose timing, storage, and missed dose; (2) participants will be asked to return the unused supplementation and bottle; and (3) the importance of contacting the study assessor will also be noted in case of any problems (e.g., unusual symptoms). Adherence to the intake of the supplements will be assessed as good, moderate, or poor by pill counts (at 2nd, 3rd, and 4th visits). Participants will also be contacted daily with the methods mentioned earlier.

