### Statistical analysis

Before statistical analysis, all data will be reviewed to check the accuracy and completeness. The primary analysis will be conducted on the intention-to-treat (ITT) population. Per-protocol (PP) and sensitivity analyses may be conducted as appropriate. The normality of data will be checked by the Kolmogorov-Smirnov test. The variables will be reported as mean ± SD or median (*Q*). The percentage changes for each variable will be separately reported and calculated by the following formula:
$$ \left[\left(E-B\right)/B\times 100\right], $$

where *E* and *B* are the end value and the baseline value of the variable, respectively.

According to the normality assumption, the significant changes between the groups will be assessed through a one-way analysis of variance (one-way ANOVA) with post hoc (LSD) analysis or Kruskal-Wallis. Changes from the baseline to post-intervention within the groups will be illustrated through a paired *t* test or Wilcoxon signed-rank test. The qualitative and quantitative variables in the two groups will be compared using the chi-square and *t* test, respectively. If necessary, the analysis of covariance (ANCOVA) will be used to control the potential confounding variables.

All analyses will be performed using a statistical software package (SPSS), version 22.0 (SPSS, Inc., Chicago, IL, USA), or NCSS2020. Statistical significance will be determined at *p* < 0.05.

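### During-intervention events sit in the exclusion criteria, and nothing reconciles them with an intention-to-treat primary analysis

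*Protocol article*

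**What the plan says.** - **Exclusion criteria.** One list opens with "The participants must not have any of the following". Among the baseline diseases and medicines it includes "taking multivitamin-mineral supplements for 3 months before or during the intervention" and "unwillingness to continue cooperation, non-compliance during the intervention (compliance less than 80" per cent).
- **Randomization and blinding.** Eligibility is settled before anything is dispensed: "After checking the inclusion and exclusion criteria and the baseline measurements by two investigators, the eligible participants will be given consecutive numbers". Those numbers then go to the pharmacist, who dispenses.
- **Participant adherence.** Adherence to the supplements is "assessed as good, moderate, or poor by pill counts (at 2nd, 3rd, and 4th visits".
- **Outcomes.** Primary and secondary outcomes are taken in every participant at baseline and day 90.
- **Statistical analysis.** "The primary analysis will be conducted on the intention-to-treat (ITT) population". A per-protocol analysis is separate and optional: "Per-protocol (PP) and sensitivity analyses may be conducted as appropriate".
- **Sample size.** The only allowance for attrition is introduced by "According to an expected 10% loss at follow-up", giving 21 per group and 84 in total.

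**The concern.** An exclusion criterion should be something that can be judged before allocation. The 80% compliance item cannot be, and neither can actual supplement use during the intervention. Unwillingness to continue also becomes a post-randomisation event whenever it arises after allocation. If such items operate as exclusions, they take randomised people out of the trial because of what they did while taking the assigned product.

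What they do may depend on that product, through tolerability or perceived benefit. The people who remain in each arm are then no longer comparable by randomisation. A comparison of those who remain is close to a per-protocol comparison, whatever it is called. At stake is who enters the primary analysis. Two sections of the article point to different answers, and if the matter is settled after data are seen, that choice is left open.

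**Working it through.** **Step 1: when can each item be judged?**

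| Item in the exclusion list | Before dispensing? | After allocation? |
|---|---|---|
| Compliance below 80% | No; the first pill count is at visit 2 (day 30) | Yes, only then |
| Multivitamin-mineral use in the 3 months before | Yes | Not applicable |
| Multivitamin-mineral use during the intervention | No, except as a stated intention | Yes |
| Unwillingness to continue | Yes, between consent and randomisation | Yes |

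The 80% item is the clear case. The during-intervention half of the supplement item is close to it. Unwillingness to continue is mixed.

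**Step 2: follow one participant through the sections.** Take someone randomised whose pill counts show 75% compliance. Under Exclusion criteria this person must not be in the trial. Under Outcomes the person is measured at day 90. Under Statistical analysis the person belongs to the primary analysis. No section says that the person stays in follow-up, or leaves only the per-protocol set.

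**Step 3: reproduce the plan's sample size.** Inputs are from the Sample size section: two-sided alpha 0.05, power 80%, (1.96 + 0.8416)² = 7.849.

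- Curcumin: (8.17² + 7²) × 7.849 / (3.64 + 7.54)² = 7.27, rounded up to 8.
- Zinc: (12.8² + 15.3²) × 7.849 / (16 − 3)² = 18.48, rounded up to 19.
- Attrition: 18.48 / 0.9 = 20.5, rounded up to 21; 21 × 4 = 84. (Starting from 19, 19 × 1.1 = 20.9 also gives 21.)

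The stated 8, 19, 21 and 84 reproduce.

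**Step 4: illustrative bias.** Let a fraction q of an arm be excluded, with a mean outcome D worse than those kept. The mean of those kept differs from the mean of the whole arm by q × D. The documents give neither q nor D, so both are assumed.

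- SD = √[(12.8² + 15.3²)/2] = 14.1 mg/dl.
- q = 0.20, D = 0.5 SD: 0.10 SD = 1.4 mg/dl, which is 11% of the 13 mg/dl planning difference.
- q = 0.20, D = 1 SD: 0.20 SD = 2.8 mg/dl, which is 22% of it.

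This is the shift in one arm's mean. In the contrast, the bias is q × D in the active arm minus q × D in the comparator. It shrinks as the two become alike and is zero if they are equal.

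**Step 5: power, as a secondary check.** Normal approximation, zinc difference 13, SD 14.1, starting from 19 per group after the planned loss; the extra exclusion rates are assumed.

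| Extra exclusion | Left per group | Pairwise power |
|---|---|---|
| 0% | 19 | 81% |
| 10% | 17.1 | 77% |
| 20% | 15.2 | 72% |
| 30% | 13.3 | 66% |

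If the factorial main effect is tested with arms pooled, power is still 91% with 13 per group.

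**The case against.** The strongest reply is that the article already names the right primary population and already plans day-90 measurement in everyone. On that view the 80% item is a discontinuation or per-protocol rule placed loosely under the wrong heading. A reader might infer that non-compliers' data are discarded and that the intention-to-treat set is really a set of compliers. The article never says so, and the benign reading is coherent. This part of the objection stands, but it does not remove the conflict: the list is worded as a bar on participation, and no section states the benign reading.

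Three further replies also stand in part.

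- A reader might take all three items as purely post-randomisation. They are not. Unwillingness can arise after consent and before allocation, and the supplement item has a valid baseline half that should stay.
- A reader might say that the 10% allowance covers none of these exclusions. People who stop cooperating are plausibly the loss to follow-up that it was meant for. Only exclusions for low compliance or supplement use fall clearly outside its wording.
- The illustrative figures rest on assumed rates. Blinding and matched placebos make similar exclusion across arms plausible, and this would reduce the bias in the contrast.

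The method for handling missing day-90 values can be left to an analysis plan and is not part of this point.

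**Conclusion.** The point holds as an unreconciled conflict between stated rules. The 80% item, and supplement use during the intervention, can operate only on people already randomised, apart from any intended supplement use declared at screening. Applied as exclusions, they would undo the intention-to-treat primary analysis and contradict outcome measurement in all participants. That much rests on the text alone.

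The documents do not support the stronger conclusion that data will be dropped, or that the primary analysis is already a complier analysis in disguise. The size of the bias is unknown. The 1.4 to 2.8 mg/dl range assumes 20% exclusion in one arm, an outcome 0.5 to 1 SD worse in those excluded, and no offsetting exclusion in the comparator. Loss of power is not the main harm: the pairwise figures depend on assumed rates, and pooled main-effect power stays above 90% throughout the range examined. The main harm is the risk of selection after randomisation.

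**What to change.** Reconcile the sections as follows.

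1. **Exclusion criteria:** keep only conditions that can be assessed before randomisation. Keep supplement use in the preceding 3 months and remove the words that extend it into the intervention. Remove the 80% compliance item. Limit unwillingness to what arises before allocation.
2. **Statistical analysis:** state that all randomised participants are followed to day 90 where they agree, whatever their pill count or supplement use, and are analysed in the group to which they were assigned.
3. **Per-protocol set:** use compliance of at least 80% and no multivitamin-mineral use during the intervention only to define this set.

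This concerns follow-up and analysis only. It takes no position on when a participant should stop taking product.

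The cost is small: a wording change, and day-90 visits that the schedule already includes. The downside is that the intention-to-treat effect may be slightly diluted by non-compliers. The Trial status section says that recruitment is under way, so the change should be dated and settled before the treatment code is opened.

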### Sample size

The sample size was determined based on the ability to detect a mean effect of FPG between the supplement and placebo groups for each supplement (curcumin or zinc), separately.

By using the following formula, the maximum sample size for curcumin group based on the trial by Chuengsamarn et al. [26] and zinc group based on the trial by Ranasinghe et al. [40] was determined to be 8 ($$ {\overline{X}}_1 $$ = 3.64, $$ {\overline{X}}_2 $$ = − 7.54, *S*_1_ = 8.17, and *S*_2_ = 7) and 19 ($$ {\overline{X}}_1 $$ = + 16, $$ {\overline{X}}_2 $$ = + 3, *S*_1_ = 12.8, and *S*_2_ = 15.3), respectively (*α* = 0.05, significance; *β* = 0.2, power). Then, the maximum sample size was considered as the final sample size, which is sufficient to evaluate the main effects. According to an expected 10% loss at follow-up, 84 subjects (21 participants in each group) will be recruited, finally.

$$ {n}_1=\frac{\left({S}_1^2+{S}_2^2\right){\left({Z}_{1-\frac{\alpha }{2}}+{Z}_{1-\beta}\right)}^2}{{\left({\overline{X}}_1-{\overline{X}}_2\right)}^2} $$

In the formula above, *S*^2^ and $$ \overline{X} $$ show the variance and the mean effect for FBS in the placebo and treatment groups, respectively. Also, for a more accurate calculation of the sample size, the WinPepi statistical program (version 11.4: Abramson, 2011) was performed.

### Randomization and blinding

The randomization of the participants for this study will be conducted using the method of block randomization with a block size of 4 using a computer-generated random number sequence by one of the research staff (who is an independent statistician and not available to the study investigators or the study staff). Then, the allocation concealment will be conducted assigning the unique codes in order to prevent “selection bias,” and it will be maintained by the pharmacist who is a research staff not involved during the study (the pharmacist is involved only with the dispensing of the investigational products). After checking the inclusion and exclusion criteria and the baseline measurements by two investigators, the eligible participants will be given consecutive numbers, which will be forwarded to the pharmacist who will dispense the interventional product. The pharmacist will open the sealed envelope (that is given by the independent statistician containing the treatment code) after the final data analysis and/or an emergency situation. All the assessments in the trial will be made by the investigators blinded to the treatment allocation. In the event of an emergency situation where being aware of the treatment allocation is critical, the pharmacist will be accessed to unblinding envelopes provided for each participant. Further assessment and required medical or legal interventions will be carried out according to the case. The emergency unblinding and the reason should be recorded in the case report form. The treatment code would be communicated to the medical personnel in charge of the treatment but should not be recorded or verbally disclosed in any of the study documents or to the patient. Since this is a double-blinded study, the investigators, participants, and those involved in the study will not be informed about the type of supplement used except the research staff. The supplements will be delivered to the participants according to the allocation on the 1st, 30th, and 60th days.

### Intervention

The dose of supplements was calculated based on the data from the previous studies [26–32, 39, 40, 44]. A dose of 30 mg/day of zinc as zinc gluconate for 3 months will be prescribed. A dose of 30 mg/day zinc element as zinc sulfate significantly improve FPG, BCF, IS, and IR for 6 months, whereas 20 mg/day of zinc element had a favorable effect on FPG, OGTT, IR, TC, LDL-C, and BCF but for 12 months. Also, the cytotoxicity of zinc gluconate was less than that of zinc sulfate. The effect of curcumin extract on the patients with IFG, IGT, and MeS has been seen with different doses ranging from 20 to 2400 mg and follow-up duration between 2 and 9 months.

Zinc supplement contains 30 mg zinc as zinc gluconate. The curcumin supplement (BCM95/Curcugreen) used in the study is an extract of dried turmeric rhizomes which was identified by a qualified botanist as *Curcuma longa*, and a voucher specimen is kept with herbarium ID HERB-ED-22. The turmeric rhizomes were extracted with ethyl acetate, and each 500-mg capsule of curcumin supplement contained 475 mg of curcuminoids and turmeric essential oil. The purity of the bioactives in the capsule was tested by HPLC, residual solvents by GCHS, and heavy metals by ICPMS, and microbial parameters conformed to the EU standards. Placebos are identical in texture and appearance to its active supplement. The placebo for zinc is made of lactose (that was produced in the School of Pharmacy, Shahid Sadoughi University of Medical Sciences and Health Services, Iran), and the placebo capsules for curcumin are made of roasted rice powder (that was produced by “M/s Arjuna Natural Pvt Ltd., India.” All participants will receive a tablet (zinc supplement or placebo for zinc) to be consumed before breakfast and a capsule (curcumin supplement or placebo for curcumin) to be taken after breakfast, daily. Also, the energy requirement of the participants will be calculated by the report of a Joint FAO/WHO/UNU Expert Consultation [45], individually. Given that the participants are overweight or obese, they will receive a standard hypo-caloric diet with at least a 7% weight loss [46] including 45–55%, 25–35%, and 10–20% of their calories from carbohydrate, fat, and protein, respectively [47].

In each visit (visit 1, 1st day; visit 2, 30th day; visit 3, 60th day), the health information (diet and physical activity) will be recommended to all participants to improve healthy habits, individually.

The recommendations will include (1) following a hypo-caloric diet, (2) avoiding excessive intake of high-fat products (whole dairy products, poultry fat (the skin of chicken), red meat, butter, cream, ice cream, processed meats (sausages), coconut oil, and palm oil), (3) avoiding excessive sugar consumption (candy, soda, syrups, sugar-loaded desserts, caramels, and chocolate), and (4) increasing PA by walking or cycling for 150 min per week [46].

The recall of the supplement intake and the routine recommendations will be given using messaging tools (Telegram and WhatsApp) daily; the telephone service will be used for the participants who are unable to get access to these tools, weekly. If supplement intake is missed in the morning, patients will be advised to take them during the same day.

